### The intervention in Davos

Children are admitted to the Dutch Asthma Center Davos for a period of six weeks in groups of four children. The children attend a school integrated into the clinic. There are also social workers who accommodate the group, and each child has his/her own mentor.

The treatment program consists of several fixed elements. Every day, a group physical activity is organized under supervision of a physiotherapist, such as fitness, swimming or outdoor activities. Weekly individual treatment sessions take place with the pediatrician, the psychologist alternating with the psychomotor therapist, and the physiotherapist (if needed). The nurse monitors correct application of topical treatment in individual sessions with each child twice daily. In these individual sessions health education is provided with a varying weekly theme. The content of the individual consultations depends on the problems described in the treatment plan. Children and their parents are separated during the six week treatment period, however parents usually visit once.

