### Sample size

The sample size calculation for the psychosocial part is based on the primary outcome coping with itch, measured with the JUCKKI, children’s itching cognitions questionnaire [23]. A difference of five points is expected between the groups on the subscale catastrophisation (negative thoughts that have gone out of control). This difference was based on a study by Staab *et al.* on the effect of educational programs in children and adolescents with AD [24]. In this study, the SD of both groups was 7.6.

An additional sample size calculation was carried out for the clinical part of the trial. This was based on the primary outcome disease activity, measured with the SA-EASI [25]. Based on the study by Staab *et al.*, in which SCORAD was used to measure disease activity, a difference of 10 points between the groups and a SD of 15 for each group was expected [24,26].

With a power of 80%, 36 children are needed in each group. Assuming a drop-out rate of 10%, 40 children will be assigned to each of the two study conditions.

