### Data collection and data analysis

In this study two sources of electronic data are used. The DECU gives a detailed overview of the intervention and follow-up period and contains the data from the questionnaires, assessments and e-consultations. Additional patient data is extracted from the electronic patient file in the Wilhelmina Children’s Hospital. After data collection, all data will be combined into one SPSS (Statistical Product and Service Solutions) database.

Data will be analyzed on an intention to treat basis. To examine whether there is a significant difference on the primary outcomes between the intervention and control group, a mixed-effects regression model will be used. Fixed effects for time, intervention group and the time*group interaction will be included in the model in order to examine the differences between the groups over time. To adjust for possible curvilinearity a squared term for time will be included in the model. A random intercept and random slope per child will be included in order to account for repeated measures within children. Baseline values of the outcome variables are included as fixed covariates to examine their possible impact on the observed treatment effect.

Data relating to asthma outcomes will be analyzed separately for all children diagnosed with asthma. All analyses conform to a specified plan. There are no interim analyses or stopping rules.

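### Davos children are treated in groups of four, but the stated model and sample size treat all children as independent; if outcomes correlate within groups, the standard error is understated

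*Protocol article*

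**What the plan says.** **Davos arm** (section on the intervention in Davos): "Children are admitted to the Dutch Asthma Center Davos for a period of six weeks in groups of four children". Social workers look after the group, there is a school in the clinic, and "Every day, a group physical activity is organized under supervision of a physiotherapist". Sessions with the pediatrician, psychologist, psychomotor therapist and nurse are individual.

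**Utrecht arm** (section on the control condition and Table 1): weekly half-day outpatient visits with individual consultations, and one group consultation in week three on coping and compliance. The size of that group is not stated.

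**Model** (Data collection and data analysis): fixed effects for time, time squared, arm and time by arm, with the baseline value as covariate. On random effects it says: "A random intercept and random slope per child will be included in order to account for repeated measures within children". No term for admission group is named.

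**Sample size**: for coping, "A difference of five points is expected between the groups on the subscale catastrophisation" and "In this study, the SD of both groups was 7.6". For disease activity, "a difference of 10 points between the groups and a SD of 15 for each group was expected". The result is "With a power of 80%, 36 children are needed in each group", and then "Assuming a drop-out rate of 10%, 40 children will be assigned to each of the two study conditions". Neither an ICC nor a design effect appears.

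**The concern.** Children in one Davos group share an admission period, peers and group staff for six weeks. Two of the three primary outcomes, coping with itch and quality of life, could plausibly be affected by the group a child happens to join. Groups are also admitted at different times over a recruitment period of more than three years, and the Background lists UV and allergen exposure among the important features of the alpine climate.

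Clustering of this kind is sustained in one arm and slight in the other, which makes the design partially nested. A model whose random effects stop at the child treats the members of a Davos group as independent. If they are not, the variance of the Davos mean is understated, intervals are too narrow and p-values are too small. The error favours a false positive finding, in a trial that is also unblinded. Because the article writes the model out, this concerns a stated rule and is not a detail left to a later plan.

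**Working it through.** **Inputs from the article.** Difference 5 with SD 7.6 (coping); difference 10 with SD 15 (disease activity); power 80%; 36 evaluable and 40 enrolled per arm; Davos groups of 4. Forty children make 40/4 = 10 Davos groups, and 36 evaluable children make about 9 groups' worth.

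**Assumptions.** Two-sided 5% test (not stated, but one-sided 5% would give 29 and 28 per arm, not 36). ICC 0 to 0.20 (not given). Each group consists of four trial participants. No clustering in Utrecht. The comparison is simplified to two means at one time point.

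**Step 1: reproduce the plan's figure.** n per arm = 2 × [SD × (1.960 + 0.842) / difference]².
- Coping: 2 × (7.6 × 2.802 / 5)² = 36.3; power at 36 per arm is 79.7%.
- Disease activity: 2 × (15 × 2.802 / 10)² = 35.3, rounded up to 36; power at 36 is 80.7%.
- Drop-out: 36 / 0.90 = 40.

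The stated figures are reproduced to rounding, with independent children and no covariates.

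**Step 2: clustering in the Davos arm only.** The design effect in Davos is 1 + (4 − 1) × ICC. The variance of the difference is multiplied by VR = [(1 + 3 × ICC) + 1] / 2, and the true standard error is √VR times the one that ignores groups.

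**Step 3: type I error of the planned test** = 2 × [1 − Φ(1.96 / √VR)].

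**Step 4: power.** Two tests must be kept apart. Let λ = (difference / SD) × √18, which is 2.79 for coping and 2.83 for disease activity.
- Planned test, uncorrected standard error: Φ((λ − 1.96) / √VR).
- Corrected test, normal approximation: Φ(λ / √VR − 1.96).

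The normal approximation ignores the small number of groups. A Welch test on Davos group means (40,000 simulated trials, 9 groups of 4 against 36 independent children) allows for it.

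| ICC | VR | √VR | Type I error, planned test | Power, planned test (coping) | Power, corrected test, normal approx. (coping / disease activity) | Power, corrected test, few groups (coping / disease activity) |
|---|---|---|---|---|---|---|
| 0 | 1.000 | 1.00 | 5.0% | 80% | 79.7% / 80.7% | 77% / 78% |
| 0.02 | 1.030 | 1.01 | 5.3% | 79% | 78.5% / 79.6% | not run |
| 0.05 | 1.075 | 1.04 | 5.9% | 79% | 76.8% / 77.9% | 73% / 74% |
| 0.10 | 1.150 | 1.07 | 6.8% | 78% | 74.0% / 75.1% | 70% / 71% |
| 0.20 | 1.300 | 1.14 | 8.6% | 77% | 68.7% / 69.9% | 64% / 66% |

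The simulated type I error of the uncorrected test was 5.8%, 6.8% and 8.4% at ICC 0.05, 0.10 and 0.20. With a group size of 3.6 (after 10% drop-out) the formula gives slightly less: 5.8%, 6.5% and 8.1%.

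**Step 5: offset from baseline adjustment.** If 7.6 and 15 are SDs of raw scores (not stated), a baseline correlation r multiplies the variance by 1 − r². The power loss in the normal approximation is fully offset when (1 − r²) × VR = 1, that is at ICC = [2 / (1 − r²) − 2] / 3.
- r = 0.3: (2 / 0.91 − 2) / 3 = 0.07.
- r = 0.5: (2 / 0.75 − 2) / 3 = 0.22.

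This bears on power only. It does not make a standard error that ignores the groups correct.

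**The case against.** A reader might infer that the standard errors are too small and the 80% power is not delivered, as plain facts. The documents do not support that, for four reasons.

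- **The ICC is unknown.** Both statements need a positive ICC and none is given. Up to about 0.02 the type I error stays near 5.3% and the corrected test loses less than 1.5 points of power.
- **The planned test loses little nominal power.** It keeps about 79%, 78% and 77% for coping at ICC 0.05, 0.10 and 0.20. The larger losses in the table belong to the corrected test and should not be paired with the inflated type I errors.
- **The 80% describes a simpler analysis.** It comes from a comparison of two means, while the planned model adjusts for baseline and uses repeated measures. Step 5 shows that a moderate baseline correlation could offset the loss.
- **Much of the Davos care is individual.** Clinical and nursing sessions are one to one, each child has a mentor, and content follows the child's own treatment plan. Features common to all Davos groups, such as the clinic school, may act on the whole arm without creating differences between groups. At six weeks and six months after treatment the correlation may also have faded.

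The Utrecht group consultation also deals with coping, so taking Utrecht as unclustered is itself an assumption.

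These objections limit the power claim and make the size uncertain. They do not justify fixing the ICC at exactly zero, which is what the stated model does, and they do not repair the type I error if the ICC is positive.

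**Conclusion.** The point holds in conditional form. The grouping, the child-only random effects and the independence assumed in the sample size are all in the article. If outcomes correlate within Davos admission groups, the true standard error is about 4%, 7% and 14% larger than the reported one at ICC 0.05, 0.10 and 0.20, with type I errors of about 5.9%, 6.8% and 8.6%. At ICC up to 0.02 the effect is negligible for practical purposes. The validity of the test is the stronger half of the point. Whether the trial ends up with less than 80% power cannot be settled from the article, because neither the ICC nor the baseline correlation is given.

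**What to change.** - Add a random effect for admission group in the Davos arm only (partially nested mixed model), with Satterthwaite or Kenward-Roger degrees of freedom.
- Check in a sensitivity analysis whether the Utrecht group consultation also induces clustering.
- State that the 80% power assumes independent children and no covariates, and give the power of the corrected test under a stated ICC. For coping without baseline adjustment this is about 73-77% at ICC 0.05 and 70-74% at ICC 0.10, the lower figures allowing for the few groups. Say that baseline adjustment may recover some or all of the loss.

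**Cost.** The change is to the analysis wording, made before the data are analysed. Enrolment and treatment stay as they are, and group membership should be recoverable from admission dates. The downside is wider intervals and a group variance estimated from about 10 groups. Even at ICC 0, allowing for so few groups brings coping power to about 77% in the group-mean simulation.

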### Control condition in Utrecht

Recently, a new multidisciplinary intervention has been developed for children with AD combining education, involvement of both dermatologists, pediatricians, psychologists and nurses, and the use of the DECU. Children are seen during half a day at the outpatient clinic on a weekly basis for a period of six weeks. During this period they have three consultations with the dermatologist, five consultations with the dermatological nurse, three consultations with the pediatric allergist and three consultations with the psychologist. The content of the individual consultations depends on the treatment goals described in the treatment plan.

In the third week a group medical appointment (also known as group consultation) is scheduled for the children and their parents separately, about coping with AD and compliance [28]. It is a substitute for an individual appointment with a clinician during which children and their parents discuss their personal experiences and advise and support each other.

A description of intervention and control conditions is provided in Table 1.

**Table 1 T1:** Overview of control and intervention conditions

	**Treatment location**	
	**Wilhelmina Children's Hospital**	**Dutch Asthma Center Davos**
Multidisciplinary team	Dermatologist, pediatric allergist, psychologist, dermatology nurse	Pediatrician, psychologist, nurse, psychomotor therapist, physiotherapist, social workers
Treatment program	Three individual consultations with dermatologist, pediatrician and psychologist	Six individual consultations with pediatrician, four with the psychologist, three with the psychomotor therapist
	One group consultation (children and parents separate)	Physical activity program under supervision of physiotherapist
Educational program	Five individual consultations with the dermatology nurse	Twice daily individual consultations with the dermatology nurse
Treatment setting	Outpatient	Inpatient
Environment	Own home in the Netherlands	Clinic in Swiss alpine environment

### Follow-up period

There is a six month follow-up period during which all children are assessed three times at the Wilhelmina Children’s Hospital: immediately after the intervention, six weeks after the intervention and six months after the intervention, which is the end of the follow-up period. During the entire follow-up period, children are encouraged to use the self-management tools in the DECU. In case of questions and/or exacerbations, they can contact the dermatology nurse with an e-consultation and, if needed, an appointment with the dermatologist is made. All children are encouraged to play sports, for example at FitKids, a Dutch organization that facilitates physical activity programs for children with a chronic disease under supervision of a children’s physiotherapist [29].

### Primary and secondary outcomes

The primary outcomes of this study are coping with itch and quality of life of the child for the psychosocial part and disease activity for the clinical part. Coping levels are measured with the JUCKKI questionnaire for children (aged 8 to 12 years) and the JUCKJU questionnaire for adolescents (aged 13 to 18 years) [23]. Quality of life is assessed with the CDQLI questionnaire [30]. Disease activity is assessed with the SA-EASI [25].

Secondary outcomes for the psychosocial part include social and emotional wellbeing of the child, feelings of autonomy and fear, quality of life and stress levels of the parents.

Secondary outcomes for the clinical part include medication use, TARC (thymus and activation-regulated chemokine), total and specific IgE (Immunoglobulin E), asthma control parameters such as FeNO (fraction of exhaled nitric oxide), ACQ (asthma control questionnaire), PAQLQ (pediatric asthma quality of life questionnaire), BHR (bronchial hyperresponsiveness) and spirometric variables such as FEV1 (forced expiratory volume in 1 second), FVC (forced vital capacity) and their ratio (FEV1/FVC). During the follow-up period, the number of flares, the number of dermatologist/pediatric/psychologist appointments, e-consultations and emergency visits or hospital admissions are recorded.

At each time point in the study, questionnaires are filled in by the child and his/her parents, blood samples are taken from the child, and lung function is assessed. A detailed overview of all parameters and measurements is provided in Table 2.

**Table 2 T2:** Study assessments

**Assessment**	**Measured with**	**T-1**	**T0**	**T1**	**T2**	**T3**
Coping with itch and disease	JUCKKI-COPECI (8-12 yr) or JUCKJU-COPEJU (13-18 yr) [23]	x	x	x	x	x
Disease-specific quality of life	CDQLI [31]	x	x	x	x	x
Disease activity and control (AD)	EASI [33]	x	x	x	x	x
	SA-EASI [25]	x	x	x	x	x
	Used topical corticosteroids	x	x	x	x	x
	TARC [34]	x	x	x	x	x
Disease activity and control (Asthma)	ACQ [35]	x	x	x	x	x
	PAQLQ [36]	x				x
	Lung function test	x	x	x	x	x
	FeNO	x	x	x	x	x
	Used medication	x	x	x	x	x
	Metacholine provocation	x	x	x	x	x
Serum	Total IgE		x			x
	Specific IgE: inhalation/food: ImmunoCAP		x			x
	Specific IgE: inhalation/food: ImmunoCAP ISAC		x			
	Eosinophils		x	x	x	x
	Cytokine profile		x	x	x	x
Questionnaires	Social demographic information	x				
	Intelligence test [37]	x				
	SF-36 [38,39]	x				
	CBCL [40,41]	x				
	Corticosteroid use	x			x	x
	NPV-J [42]	x				
	TRF [40]	x				
	CBSK/CBSA [43,44]	x		x		x
	ZBV-K [45]	x	x	x		x
	PUL (>12 yr) [46]	x		x		x
	Quality of life (parents) [47]	x	x	x		x
	ZBV [48]	x		x		x
	NOSI-K [49]	x		x		x
	NOSI-events [49]	x				x
Other	Maximal cycle ergometer test	x				x
	Bacterial colonization of the skin		x	x	x	x
	Bacterial colonization of the nose		x	x	x	x
	Skin strips for protease activity		x	x	x	x

ACQ, asthma control questionnaire; CBCL, child behavior checklist; CBSK, self-perception profile for children; CBSA, self-perception profile for adolescents; CDQLI, the children’s dermatology life quality index; COPEKI/COPEJU, coping with disease questionnaire; EASI, eczema area and severity index; FeNO, fraction of exhaled nitric oxide; IgE, Immunoglobulin E; ImmunoCAP, ImmunoCAP system (Thermo Fisher Scientific, Uppsala, Sweden); ImmunoCAP ISAC, Immunosolid-phase allergen chip (Thermo Fisher Scientific, Uppsala, Sweden); JUCKKI/JUCKJU, itching cognitions questionnaire; NOSI-events, parental stress index-events; NOSI-K, parental stress index- short form; NPV-J, Dutch personality questionnaire-youth version; PAQLQ, pediatric asthma quality of life questionnaire;

PUL, positive outcome list; SA-EASI, self-administered eczema area and severity index; SF-36, short form health survey; TARC, thymus and activation-regulated chemokine; T-1, assessment at start of participation in trial; T0, assessment before start of the intervention; T1, assessment direct after the intervention; T2, assessment six weeks after the intervention; T3, assessment six months after the intervention; TRF, teacher report form; ZBV, state-trait anxiety inventory; ZBV-K, state-trait anxiety inventory for children.

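### The coping sample size is stated for the child questionnaire only, while adolescents complete a different form and the listed model terms include neither form nor age

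*Protocol article*

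**What the plan says.** Three places in the protocol article bear on this.

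- **Primary and secondary outcomes.** The form depends on age: "JUCKKI questionnaire for children (aged 8 to 12 years) and the JUCKJU questionnaire for adolescents (aged 13 to 18 years". Table 2 repeats the split and schedules the coping questionnaire at all five assessments, T-1 to T3. Eligibility runs from 8 to 18 years, so both forms will be in use.
- **Sample size.** The psychosocial calculation "is based on the primary outcome coping with itch, measured with the JUCKKI"; the JUCKJU is not mentioned. The planning figures are: "A difference of five points is expected between the groups on the subscale catastrophisation", and "In this study, the SD of both groups was 7.6". They come from an external study "on the effect of educational programs in children and adolescents with AD". The article does not say which form or age group produced the 5 and the 7.6. A second calculation, for the SA-EASI, states that "a difference of 10 points between the groups and a SD of 15 for each group was expected". The result is 36 per group at 80% power, or 40 after 10% drop-out.
- **Data collection and data analysis.** For the primary outcomes, "a mixed-effects regression model will be used". The listed terms are time, group, their interaction, squared time, a random intercept and slope per child, and the baseline value. Neither form nor age is listed. Under Randomization, allocation is controlled for age and asthma diagnosis.

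**The concern.** The calculation counts every evaluable child in the arm, but its inputs are given for a form that only the 8 to 12 year-olds complete. Either the same difference and SD are assumed for the adolescent form, or the inputs do not describe the sample to which they are applied. The article does not say which.

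Three things are at stake if the forms differ in level, spread or range:

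- a pooled difference in points has no clear unit;
- the residual variance contains differences between forms that no listed term removes directly;
- a child whose form changed on turning 13 would have a baseline on one instrument and follow-up on another.

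Age, which largely determines the form, is a randomisation factor but not a listed model term.

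**Working it through.** **Inputs.** From the Sample size section: difference 5 and SD 7.6 for coping; difference 10 and SD 15 for SA-EASI; power 80%; 36 evaluable per arm. Assumed here, because the article does not give them: two-sided alpha 0.05, and the share of children on each form.

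**1. The plan's own figure.** n per arm = 2(1.960 + 0.842)² (SD/difference)².

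- Coping: 2 × 7.849 × (7.6/5)² = 36.3, rounded up to 37.
- SA-EASI: 2 × 7.849 × (15/10)² = 35.3, rounded up to 36.
- Drop-out: 36/0.9 = 40.

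The stated figures reproduce to within one child. Power at 36 per arm is Φ(difference/(SD × √(2/36)) − 1.96). For coping this is Φ(2.791 − 1.96) = 79.7% (78.6% by the t-test). For SA-EASI it is 80.7%. So the coping calculation needs the whole arm.

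**2. If 5 and 7.6 hold on both forms.** The standardised effect is 5/7.6 = 0.66 and power stays at 79.7% for the whole sample.

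**3. If they do not.** Assume half the children are on each form and scores are pooled in points, with no baseline adjustment.

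| Departure on the JUCKJU | Pooled quantity | Power |
|---|---|---|
| Mean shifted by 4 / 6 / 8 points | SD √(7.6² + 0.25 × shift²) = 7.86 / 8.17 / 8.59 | 77% / 74% / 70% |
| SD 10 / 12, difference still 5 | SD √(0.5 × 7.6² + 0.5 × SD²) = 8.88 / 10.04 | 67% / 56% |
| SD 5, difference still 5 | SD 6.43 | 91% |
| Difference 4 / 3 / 2, SD still 7.6 | mean difference 4.5 / 4.0 / 3.5 | 71% / 61% / 50% |

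These rows differ in what scaling can repair.

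- A pure level shift is removed by a form term or by centring within form.
- With SD 12 and a difference of 5 on the JUCKJU, scaling within form gives a mean effect of 0.5 × 5/7.6 + 0.5 × 5/12 = 0.537 SD. Power is then Φ(0.537/0.2357 − 1.96) = 63%, against 56% in points.
- If the JUCKJU is only a stretched scale (SD 12, difference 5 × 12/7.6 = 7.89), pooling in points costs little. The mean difference is 6.45, the SD 10.04 and power 78%.
- A smaller true effect in adolescents at the same SD (last row) is not recovered by any rescaling.

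**4. Children who turn 13.** T0 to T3 is six weeks plus six months, about 32 weeks. With ages spread evenly over the 11 year-groups from 8 to 18, (32/52)/11 = 5.6% turn 13 in that time, about 4 of 72. The even spread is an assumption, and the time from T-1 to T0, which is not given, would add to it.

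**The case against.** The case against making much of this has several parts, and most of them stand.

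- A reader might infer that raw JUCKKI and JUCKJU scores will be entered together. The article does not say so. It refers to a specified analysis plan that is not shown, and a scoring rule may be there.
- A reader might also infer that the 80% power applies to only part of the sample. That is wrong: about 80% needs all 36 per arm. If the forms are comparable, it applies to everyone. If 5 and 7.6 describe the JUCKKI alone, a test in 8 to 12 year-olds would have 33% to 65% power if they make up 30% to 70% of the sample. The article plans no such test and gives no age split, so these figures are not a power loss of the planned analysis.
- The article defines both forms jointly as the itching cognitions questionnaire, with one reference, and the planning study covered children and adolescents. This leans towards comparable forms but does not establish a common scale.
- Age-controlled randomisation should roughly balance the forms between arms. The baseline covariate and random intercept absorb much of a stable level difference, so the level-shift figures above are upper limits on the loss. Confounding is not the issue.
- It might be inferred that children change form at 13. The article gives no rule either way.
- The SA-EASI calculation gives 36 per group on its own.

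What remains is a mismatch in the article's own text: the stated inputs name one form, the measurement section uses two, and the listed model terms do not distinguish them.

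**Conclusion.** The point holds as a modest and inexpensive improvement. It does not show that the sample size is wrong or that the comparison is biased. The stated power for coping rests on an unstated assumption that a 5-point difference and an SD of 7.6 hold on both forms. Under that assumption power is about 79 to 80% at 36 per arm. Without it, the effect in points is hard to interpret and some power may be lost. How much depends on how the forms differ, which the article does not show, and the table gives a range rather than an estimate. N need not change. The conclusion rests on a two-sided 0.05 test, an illustrative equal split between forms, and a single-time-point comparison in place of the planned repeated-measures model.

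**What to change.** 1. Score catastrophisation in SD units within form, dividing by the baseline SD computed over both arms together, without reference to allocation.
2. Add form (age group at entry) to the mixed model as a fixed effect. This also brings a randomisation factor into the analysis.
3. Assign the form at T-1 and keep it to T3, so that each child's baseline and follow-up use the same instrument.
4. Restate the planning effect as 5/7.6 = 0.66 SD, assumed for both forms, giving about 79 to 80% power at 36 per arm (two-sided 0.05 assumed). Say which form or age group supplied the 5 and the 7.6, and whether 7.6 is the SD of a score or of a change. The conversion to baseline SD units is direct only for the former.

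The cost is a few lines of analysis wording and one rule in the data-collection portal; recruitment was still open when the article was written. There are two drawbacks. The effect is reported in SD units, so the point difference within each form should be shown beside it. A few children who turn 13 will also finish on the child form. If the analysis plan already shows that the forms share a scale, item 4 and the rule in item 3 are enough.
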